## 4. GENERAL METHODOLOGY AND CONVENTIONS

### 4.1. Hypotheses and Decision Rules

There will be no formal hypothesis testing in this study.

#### 4.1.1. Maximum Tolerated Dose Determination

*Determination of MTD will be performed using a Per-protocol analysis set (evaluable for MTD).*

##### Bayesian adaptive approach:

*The dose escalation in Part 1A, and dose finding in Part 1B [REDACTED] of the study will be guided by a Bayesian analysis of Cycle 1 DLT data for PF 07248144 as a monotherapy (Part 1A) or in combination (Part 1B, [REDACTED]). A traditional 2-parameter BLRM will be used to model the dose/DLT relationship of PF 07248144 monotherapy. A more complex BLRM model specifically designed for combinations will be used to model the dose/DLT relationship of PF-07248144 given in combination with fulvestrant, [REDACTED]*

*Using DLT data at all tested dose levels and pre specified prior distribution of model parameters, the posterior distribution for probability of having a DLT will be calculated for all dose levels. The dose escalation in Part 1A, Part 1B [REDACTED] of the study will be guided by a Bayesian analysis of Cycle 1 DLT data for PF-07248144 as a monotherapy (Part 1A) or in combination (Part 1B [REDACTED]). A traditional 2-parameter BLRM (Neuenschwander, et al. 2015) will be used to model the DLT relationship of PF-07248144 monotherapy and a more complex BLRM model specifically designed for double [REDACTED] combinations will be used to model the dose toxicity relationship of PF-07248144 given in combination with fulvestrant [REDACTED]. Using DLT data at all tested dose levels and pre specified prior distribution of model parameters, the posterior distribution for probability of having a DLT will be calculated for all dose levels.*

##### Assessment of participant risk:

*After each cohort of participants, the posterior distribution for the risk of DLT for new participants at different doses of interest for PF-07248144 will be evaluated. The posterior distributions will be summarized to provide the posterior probability that the risk of DLT lies within the following intervals:*

|                  |              |
|------------------|--------------|
| Under-dosing:    | [0, 0.16]    |
| Targeted dosing: | [0.16, 0.33] |
| Overdosing:      | [0.33, 1]    |

### The EWOC principle:

*Dosing decisions are guided by the escalation with overdose control principal. A dose may only be used for newly enrolled participants if the risk of excessive toxicity at that dose*

### Prior distributions:

*Weakly informative prior distributions based on pre-clinical/expert opinion information will be chosen for the logistic parameters for prior distribution in Part 1A, see Appendix 9 of the protocol.*

*A MAP approach might be used to derive the prior distribution for model parameters used in Part 1B, based on the data collected in Part 1A and DLT data collected in clinical studies for fulvestrant, . The MAP prior for the logistic model parameters for this study is the predictive posterior distribution of the parameters given the historical data. MAP priors are derived from hierarchical models, which take into account possible differences between the studies. A full description of the application of the MAP approach to derive the prior distributions of the model parameters is given in a Technical Supplement.*

*In case of change of the dosing regimen, DLT data accumulated during the dose escalation with the original regimen may be used to form a prior for further BLRM analysis. Details about derivation of this prior using MAP approach is given in a Technical Supplement.*

### Starting dose:

*The starting dose of Part 1A is 8 mg QD. For this dose the prior risk of overdosing is 10.1%, which satisfies the EWOC criterion. A full assessment of the prior risk to participants is given in Appendix 9 of the protocol.*

### Sensitivity Analysis:

*To mitigate the risk of dichotomizing and misclassifying DLTs, a sensitivity analysis that uses weighted DLT/AE data (in equivocal cases) into the BLRM model estimation will also be performed. If all the investigators and the sponsor agree on the equivocal DLT/AE data, the DLT weighting approach could be the primary dose escalation method. See Appendix 9 of the proptocol for more details.*

### Stopping Criteria:

*The maximum number of participants in dose escalation part of the trial is set to 40. The trial will be stopped when the following criteria are met:*

- *At least 6 participants have been treated at the recommended MTD/RP2D.*
- *The dose  $\tilde{d}$  satisfies one of the following conditions:*
  - *The probability of target toxicity at dose  $\tilde{d}$  exceeds 50%, ie,  $\Pr(0.16 \leq \pi_{\tilde{d}} < 0.33) \geq 50\%$ .*
  - *A minimum of 12 participants have been treated in the trial.*

*These stopping criteria are applicable to Part 1A, Part 1B, [REDACTED]*

## **4.2. Sample Size Determination**

*The total number of participants is estimated to be approximately 145 to 190.*

### **4.2.1. Part 1 Dose Escalation**

*Approximately 70 participants will be enrolled in Part 1 including 25 to 30 participants in Part 1A, 6 to 9 participants in Part 1B, [REDACTED]. The actual number of participants enrolled will depend on the tolerability of PF-07248144 and the number of dose levels required to identify the MTD/RDE as monotherapy or in combination.*

### **4.2.2. Part 2 Dose Expansion**

**Part 2A:** *Approximately 30 participants will be enrolled in Part 2A.*

*Assuming a non informative prior (ie, Jeffrey's prior) if 9 out of 30 participants have tumor response, this would predict a posterior probability (Beta Binomial) equal to [REDACTED] that the true response is not inferior to target response rate of [REDACTED] and a posterior probability equal to [REDACTED] that the true response is inferior to benchmark rate of [REDACTED].*

**Part 2B:** *Approximately 30 participants will be enrolled in Part 2B.*

*Assuming a non informative prior (ie, Jeffrey's prior) if 9 out of 30 participants have tumor response, this would predict a posterior probability (Beta Binomial) equal to [REDACTED] that the true response is not inferior to target response rate of [REDACTED] and a posterior probability equal to [REDACTED] that the true response is inferior to benchmark rate of [REDACTED].*

*Participants from Part 1A and Part 1B [REDACTED] who were treated at the dose level selected for Part 2 and fulfilling Part 2 inclusion/exclusion criteria may be counted towards the sample size of Part 2 at the corresponding regimen (monotherapy and combination).*

[REDACTED]

[REDACTED]

[REDACTED]

[REDACTED]

[REDACTED]

*Participants from Part 1A, Part 1B, [REDACTED] who were treated at the dose level selected for Part 2 and fulfilling Part 2 inclusion/exclusion criteria may be counted towards the sample size of Part 2 at the corresponding regimen (monotherapy and combination).*

### 4.3. General Methods

The data will be summarized by dose level, defined by the initial dose of the study intervention administered to participants. If a dose level has more than 1 cohort, data from these cohorts will be combined. DLT rates at the study dose levels will be presented via mean and medians and a Bayesian credible interval based on the posterior density from the full probability model. This information will also be used for the dose level review meetings (DLRM) to guide the dose escalation.

#### 4.3.1. Analyses for Binary Endpoints

Binary data will be summarized using number of unique participant incidence, proportion in the analysis set, and the 2-sided 95% exact confidence interval for the proportions. The confidence interval will be based on the Clopper-Pearson exact method.

#### 4.3.2. Analyses for Continuous Endpoints

Continuous data will be summarized with the mean, median, minimum, maximum, standard deviation, and 2-sided 95% confidence interval of the mean if the sample size permits and deemed necessary.

#### 4.3.3. Analyses for Categorical Endpoints

Categorical data will be summarized by number of unique participant incidence and proportion of participant in each category, and 2-sided 95% confidence interval of the proportion if the sample size permits and deemed necessary.

#### 4.3.4. Analyses for Time-to-Event Endpoints

The time-to-event endpoints will be summarized using the Kaplan-Meier method and estimated survival curves may be displayed graphically when needed. Graphs will describe the number of participants at risk over time. The median, quartiles, and probabilities of an event at particular points in time will be estimated by the Kaplan-Meier method, when possible based on the number of observed events. Confidence intervals for medians and quartiles, based on the Brookmeyer-Crowley method (Brookmeyer and Crowley 1982), may be presented. Confidence intervals for the estimated probability of an event at a particular time point may be generated using the Greenwood formula.

For the analysis of safety endpoints, the sponsor data standard rules for imputation will be applied based on Pfizer Safety Rulebook.

In compliance with Pfizer standards, if the day of the month is missing for any date used in a calculation, the 1st of the month will be used to replace the missing date unless the calculation results in a negative time duration (eg, date of onset cannot be prior to day one date). In this case, the date resulting in 0 time duration will be used. Pfizer standards are also used if both month and day are missing (Jan 1 unless negative time duration). This excludes the pharmacokinetic and ECG analyses, which will only use the actual date collected or if date not available deem the data missing.

For binary efficacy endpoint related to tumor assessment , every effort will be made to retrieve data in the CRF, however missing data will be left as is, no imputation will be performed. The reasons for missing tumor assessment will be collected.

For the time-to-event endpoints, the missing data handling method will be censoring. Censoring rules for time-to-event endpoints are detailed in [Section 8.1](#).

[REDACTED]

[REDACTED]

[REDACTED]

[REDACTED]

[REDACTED]

[REDACTED]

[REDACTED]

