### 5.4. Efficacy Endpoint(s)

BOR, DOR, CBR, and PFS as assessed by investigator based on RECIST v1.1, are exploratory endpoints in Part 1 to evaluate the anti-tumor activity of PF-07248144. They, along with TTP, as assessed by investigator based on RECIST version 1.1, and Overall Survival are secondary endpoints in Part 2.

*Full Analysis Set will be used for all response related analyses including BOR, PFS, TTP, and OS. DOR will be analyzed only on responders.*

*Tumor response will be presented in the form of participant data listings that include, but are not limited to tumor type, dose on Day 1, tumor response at each visit, and best overall response. Proportion of participants responding to the treatment will be presented for each dose level.*

*For prostate cancer only, PSA and bone scan monitor, report and analysis should follow PCWG3 guidelines (see Protocol) Existing or new bone lesions as assessed by radionuclide bone scan will be described and documented.*

*PSA data will be presented in form of listings that include dose on Day 1, measurement, and % change from baseline at visit.*

*Part 1A, Part 1B, [REDACTED] Progression date, date of first response, last tumor assessment date, and date of last contact will be listed.*

*Part 2: The Kaplan-Meier method will be used to analyze all time to event endpoints. Median PFS (if reached) will be calculated. DOR will be listed. Efficacy data of participants from Part 1A, Part 1B, [REDACTED] treated at the dose level selected for the corresponding expansion cohort and satisfying inclusion/exclusion criteria might be included in the analysis of efficacy endpoints of Part 2.*

Part 1 and Part 2 data will be summarized separately, and may also be pooled together for analysis if deemed necessary, eg, to account for food effects subgroups. Specifically, the key tables in Part 2 include:

1. BOR is the best response recorded from the randomization until disease progression or death due to any cause. This is derived from the sequence of objective statuses. Objective statuses are not considered after objective progression is documented or after start of the first anticancer treatment post discontinuation of protocol treatment. BOR for each patient will be derived as one of the following categories.
  - Complete Response (CR): Two objective statuses of CR a minimum of 4 weeks apart documented before progression.

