| No PD                                                                                                                                                                                                                                                   |                                                                                                                                    |                       |
| New anti-cancer therapy given prior to PD or death                                                                                                                                                                                                      |                                                                                                                                    |                       |
| a If the patient dies ≤17 weeks after ‘start date’ and did not initiate new anti-cancer therapy, the death is an event with date on death date.                                                                                              |                                                                                                                                    |                       |
| b If there are no adequate post-baseline tumor assessments prior to the PD or death, then the time without adequate assessment should be measured from the ‘start date’; if the criteria were met the censoring will be on the ‘start date’. |                                                                                                                                    |                       |
| Note: If no adequate tumor assessment within 17 weeks after ‘start date’ then censor at ‘start date’.                                                                                                                                                   |                                                                                                                                    |                       |

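### The first-of-month (or 1 January) rule for partial dates can place a new therapy before the progression that preceded it, or a death before the last known-alive date, because only a negative duration stops it

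*Protocol*

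**What the plan says.** The rule stands in the SAP's text on missing dates (4.4.1 in its table of contents).

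- **Scope:** it applies "if the day of the month is missing for any date used in a calculation".
- **Replacement:** the 1st of the month "will be used to replace the missing date unless the calculation results in a negative time duration". For a date known only by year: "Pfizer standards are also used if both month and day are missing (Jan 1 unless negative time duration".
- **Guard:** the one example is that "date of onset cannot be prior to day one date". When the guard acts, "the date resulting in 0 time duration will be used".
- **Exemption:** "This excludes the pharmacokinetic and ECG analyses, which will only use the actual date collected".

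The same section says that missing data for time-to-event endpoints are handled by censoring, and refers to SAP 8.1. In Table 2 there, "New anti-cancer therapy given prior to PD or death" leads to censoring at the last adequate assessment; Table 3 does the same for TTP. OS (SAP 5.4) runs from start of treatment to death. The last-contact date must come from complete, non-imputed dates, but it is derived only for participants not known to have died. SAP 2.4 closes the on-treatment safety window at the earlier of 28 days after the last dose and the day before new anticancer therapy.

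**The concern.** A rule that always picks the earliest possible date is not neutral when the order of two dates decides the outcome. Progression commonly leads to the next therapy, sometimes within the same calendar month. If the day of that therapy is unknown, the rule can move it ahead of the PD. The PD is then lost as an event, which pushes PFS and TTP upward.

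For OS the error runs the other way: an imputed death is moved earlier or left where it was, never later. The result can contradict visits or calls that the trial itself recorded. Survival follow-up in Part 2 is by telephone about every 3 months, so death dates depend on what is reported at a call.

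With about 30 participants per expansion cohort, one or two reordered records are visible in a Kaplan-Meier curve.

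**Working it through.** The plan gives no figure for this point, so there is none to reproduce. The check applies the stated rule to dates.

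**1. Does the guard act?** PFS, TTP and OS all run from start of treatment. None of them computes the interval from PD to new therapy, or from last contact to death. A therapy or death date imputed after day one therefore gives a positive duration, and the guard stays silent.

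**2. PFS and TTP example (8-weekly scans as in the protocol's Schedule of Activities).**
- Start is 28 Mar 2022. The week-16 scan is 18 Jul (day 113) and the week-24 scan is 12 Sep (day 169), showing PD.
- New therapy truly starts 22 Sep and is recorded as Sep 2022. It is imputed to 1 Sep, 157 days after start.
- 1 Sep precedes 12 Sep, so PFS and TTP become censored at day 113 instead of events at day 169.
- On-treatment window, assuming last dose on 12 Sep: true end = min(12 Sep + 28 days = 10 Oct, 22 Sep − 1 day) = 21 Sep. With the imputed start the end is 31 Aug, 21 days earlier and before the last dose.

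**3. OS examples.**
- Last contact 20 May, death recorded only as May (truly 27 May): imputed 1 May, 19 days before a date when the participant was known alive and 26 days early.
- Last contact in October, death known only by that year: imputed 1 January, about 9 months before last contact.
- Start in March, death known only by the same year: 1 January precedes day one, the guard acts, and OS becomes zero.

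**4. How often the order reverses.** With the day missing and a true gap of g days, an imputed date falls before its anchor (PD or last contact) when both dates share a month and the anchor is not on the 1st. In a month of m days that is max(0, m − g − 1)/m of anchor days; for m = 30 and g = 14 it is 15/30 = 50%. Counting all 1,461 days of 2021–2024, with the guard not triggered:

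| True gap (days, assumed) | Day missing | Day and month missing |
|---|---|---|
| 3 | 87% | 99% |
| 7 | 74% | 98% |
| 14 | 51% | 96% |
| 21 | 28% | 94% |
| 28 | 5% | 92% |
| 42 | 0% | 88% |

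Before any guard, an imputed death is early by 14.7 days on average (maximum 30) with the day missing, and by 182 days on average (maximum 365) with day and month missing.

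**5. Cohort-level illustration.** The share of progressors whose next-therapy date lacks the day is an assumption: 10, 20 or 30%. With a 14-day gap, the share of PD events lost is 0.51 times that, or about 5, 10 and 15%. A simulation with n = 30, exponential PFS with median 24 weeks and gaps varying around a 14-day median moved the 24-week PFS estimate up by roughly 1 to 5 points over that range. The standard error at that point is √(0.5 × 0.5/30) ≈ 9 points.

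**The case against.** **The rule may be meant for safety dates.** It follows a sentence on safety endpoints, its example is an onset date, and the contents list a separate efficacy subsection (4.4.2). But its wording covers every date in a calculation and names the two exemptions, PK and ECG. The censoring sentence does not help: it sends the reader to tables that themselves depend on the therapy date. Company standards outside the documents and redacted lines could contain a bound; the visible text has none.

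**Day one is only an example of the guard.** This stands. A reader might infer that the guard is confined to day one, but the text bars any negative duration. How it would apply to an interval that no endpoint computes is left open.

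**Reversed dates would often be noticed.** The protocol forbids other antitumor treatment during study treatment and places the end-of-treatment visit before any new therapy. A therapy start dated during ongoing dosing would look wrong in review. That makes silent propagation less likely but does not change the rule.

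**The frequency is assumed and the effect is small.** Both stand. No partial-date rate or gap is documented. Deaths in the active collection period are reported as SAEs within 24 hours, which favors complete dates there. The illustrated shift in 24-week PFS is well below the sampling error, and there is no hypothesis test.

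**Response is not affected.** A reader might infer that losing the PD also distorts the response results. SAP 5.4 says "Objective statuses are not considered after objective progression is documented or after start of the first anticancer treatment post discontinuation of protocol treatment". If the earlier scan already qualified as SD, best response stays SD. If the PD was at the first scan, it may become not evaluable. Both PD and not evaluable are non-responses in the Full Analysis Set, so the objective response rate is unchanged.

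**Conclusion.** The point holds as a conditional one. As written, the rule can turn a documented PD into censoring for PFS and TTP, can shorten the on-treatment window, and can date a death before a known-alive date or at day one. For each affected date the direction is fixed: a PFS or TTP event is lost, or OS is shortened.

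A reader might infer that the rule routinely does this, or that PFS is inflated by a known amount. The documents do not support either. Reversal needs both dates in the same month, or in the same year when the month is missing. The size rests on gaps and partial-date rates that are assumed here: per affected day-missing date the chance runs from 87% at a 3-day gap to 0% at 42 days.

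PFS, TTP and OS are secondary in Part 2, and PFS is exploratory in Part 1. The primary adverse-event summaries are touched only through the SAP 2.4 window. It is worth correcting because a stated rule produces impossible or reversed orderings and the correction is cheap.

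**What to change.** Exempt death and new-anticancer-therapy dates from the unbounded rule in SAP 4.4.1, and state instead:

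- **Partial death date:** the later of (last known-alive date + 1 day) and the first day of the known month or year.
- **Partial new-therapy start:** the later of (last study dose + 1 day) and the first day of the known month or year. Move it to no earlier than the PD date only when the recorded reason for ending treatment is objective progression and the PD lies within the known month or year. An unconditional bound at PD would create false events for participants who stopped for another reason, such as global deterioration, and truly began new therapy before a later PD scan.
- **Cap:** no imputed date may pass the end of the known month or year.
- **Consistency:** use the same bounded therapy date for the on-treatment window in SAP 2.4.

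In the PFS example, with last dose on 12 Sep, the therapy start becomes 13 Sep, PFS stays an event at day 169, and the window ends on 12 Sep rather than 31 Aug. In the May death example, the death becomes 21 May, 6 days early instead of 26. Imputed deaths can still be early, but not before a known-alive date.

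The cost is a few sentences in the SAP and a small programming change. No new data are needed.
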